Based on the sample size calculations, with an alpha value of 0.05 and a power of 80%, a total of 850 patients have been recruited to the study, with 425 patients in each arm. Estimates of sample size were made based on the percentage of delirium-free assessments (the primary outcome) and, secondarily, the ICU LOS. LOS was chosen in addition to the percentage of delirium-free assessments as a significant relationship between delirium and LOS has been observed. Delirium assessment is by its nature subjective and the investigators wished to also allow the study to be powered to detect a reduction of LOS of 1 day (as an objective patient-orientated outcome). An audit of 100 patients across the two primary sites was used to provide preliminary data to guide sample size calculations where an average of 54% of assessments were deemed delirium free (standard deviation of ± 45%). The research group is interested in being able to detect a 10% increase in the percentage of delirium-free assessments. This would require a sample size calculation of 319 per group. Adjustment for non-parametric data (15%) increases this to 367 per group. It is expected that up to 10% of patients recruited in the study will not be assessable for delirium at any point during the study. To account for this, and missing data/loss to follow-up, the sample size was increased by 15% to 423 patients per group (total rounded to 850).

To detect a change in LOS of 1 day, using a sample size calculation for a gamma distribution, 387 patients per group would be required. The greater number of 850 was selected to have enough power to answer both questions. The formula used to calculate sample size was that described by Wand and Chow in 2007 [27].

The framework of the study is of superiority of melatonin over placebo for the prevention of delirium. Superiority analyses will be two-sided and considered statistically significant at the 5% level.

The DSMC is comprised of an independent intensivist, an epidemiologist, and a statistician independent of the trial statistician. The independent DSMC will review all serious adverse events and perform an interim analysis after 400 patients using the Haybittle-Peto stopping rule. The Haybittle-Peto stopping rule states that if an interim analysis shows a probability of equal to or less than 0.001 that a difference as extreme or more between the treatments is found, given that the null hypothesis is true, then the trial should be stopped early [28].

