## Analysis

Primary and secondary outcomes will be analysed as described below. Where appropriate, analysis of primary and secondary outcomes will be analysed by a number of predetermined subgroups. These subgroups will include (1) percentage of delirium-free assessments by age: less than 65 or more than 65 years of age; (2) percentage of delirium-free assessments by gender; (3) percentage of delirium-free assessments by delirium subgroup at baseline: hyperactive, hypoactive, and mixed, as well as no delirium; (4) percentage of delirium-free assessments by diagnostic category (respiratory, cardiovascular, gastrointestinal, toxicological, neurological, metabolic, sepsis, trauma, traumatic brain injury); and (5) percentage of delirium-free assessments by > 50% risk or < 50% risk as per Pre-Deliric Score (calculated from first 24 h of ICU admission). Multiplicity adjustments will not be made.

For the primary outcome of percentage of delirium-free episodes, patients will be assessed for delirium twice a day for 14 days or until they are discharged from ICU, whichever occurs first. The CAM-ICU tool will be used to assess delirium, with a result recorded as either ‘positive’ or ‘negative’ for delirium. The assessment will be carried out by trained ICU medical or nursing staff. The percentage of delirium-free assessments will be calculated for each participant. The percentage of delirium-free assessments for participants in each group will then be compared using Student’s *t* test. It is assumed that the data will be normally distributed. If the distribution of the data is not normally distributed, alternative approaches will be considered; however, the initial plan is robust to deviations from normality with this sample size. Supporting analysis will use linear regression making adjustments for baseline covariates.

A secondary analysis will look at the rates of delirium in each group. The number of times an individual is reported as being positive for delirium and the total number of assessments will be examined by a comparison of rates. In addition, a Poisson regression will be used with the number of positive delirium assessments reported and offset the total number of assessments. Baseline characteristics will be included as covariates in the model. The covariates will include age, gender, delirium subtype, diagnostic category, and Pre-Deliric score.

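### The secondary Poisson regression of positive CAM-ICU assessments has no allowance for overdispersion, although the plan's own audit shows that the Poisson variance cannot hold

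*SAP article*

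**What the plan says.** The Analysis section of the SAP article describes two secondary analyses of positive CAM-ICU results. In the first, each patient's positive count and "the total number of assessments will be examined by a comparison of rates"; no test is named. In the second, "a Poisson regression will be used with the number of positive delirium assessments reported and offset the total number of assessments". The Poisson model is to be adjusted for age, gender, delirium subtype, diagnostic category and Pre-Deliric score. The section specifies no variance estimator, dispersion parameter, alternative count distribution or random effect for either analysis.

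A random individual effect does appear in the plan, but under the heading Severity and duration of delirium. It governs the analyses listed there, not the two described above.

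The sample-size paragraph in Study methods reports an audit of 100 patients in which "an average of 54% of assessments were deemed delirium free (standard deviation of ± 45" percentage points). Statistical principles sets P < 0.05 and 95% confidence intervals without exempting secondary analyses.

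**The concern.** A Poisson model fixes the variance of each patient's count at its mean. That cannot hold when a patient's repeated assessments are strongly alike, because the counts then spread much more widely between patients than Poisson allows. With one row per patient, this is overdispersion caused by within-patient correlation.

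The audit points to strong correlation. The largest possible SD of a proportion with mean 0.54 is √(0.54 × 0.46) = 0.498, and the audit SD is 0.45. Most patients must therefore have been nearly always positive or nearly always negative. The plan sizes the trial on a spread that its secondary count model does not allow for.

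At stake is the credibility of a rate ratio that will be read beside the primary result and that uses the same CAM-ICU data. If its standard error is too small, a null t test could stand next to a rate ratio that appears significant only because its interval is too narrow.

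**Working it through.** **Inputs from the SAP article**

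- Study methods: "an average of 54% of assessments were deemed delirium free", so the mean positive proportion is 0.46; SD 0.45.
- Study methods: "with an alpha value of 0.05 and a power of 80" percent; "Superiority analyses will be two-sided and considered statistically significant at the 5% level".
- Study methods: the aim is to "detect a 10% increase in the percentage of delirium-free assessments"; "a total of 850 patients have been recruited to the study, with 425 patients in each arm".
- Analysis: two assessments a day for at most 14 days, so at most 28 per patient.
- Trial population: expected stay of at least 72 h, which suggests about 6 assessments. This is an assumption, because the article gives no mean number. Enrolment up to 48 h after admission means that some patients may have fewer.

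**Step 1: reproduce the plan's figure.** n per group = 2 × (1.960 + 0.842)² × 45² / 10² ≈ 318, against 319 stated. Then 319 × 1.15 = 366.9 (367) and 367 × 1.15 = 422.05 (423). This confirms that 45 points is the SD between patients of the per-patient percentage.

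**Step 2: compare variances.** Audit variance of a patient's rate: 0.45² = 0.2025. Poisson variance: 0.46/m. Dispersion φ = 0.2025 × m / 0.46. The model-based standard error is too small by √φ, and the actual two-sided error is 2[1 − Φ(1.96/√φ)].

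**Step 3: no covariates.** The simulation column uses beta-binomial counts with per-patient SD 0.45, 425 per arm, no treatment effect and 3,000 runs.

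| m | φ | √φ | Type I error, formula | Simulated |
|---|---|---|---|---|
| 3 | 1.32 | 1.15 | 8.8% | not run |
| 6 | 2.64 | 1.63 | 22.8% | 23.1% |
| 14 | 6.16 | 2.48 | 43.0% | 42.6% |
| 28 | 12.33 | 3.51 | 57.7% | 58.3% |

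With variable stays the simulated error was 33% (2–14 assessments, mean 8) and 48% (2–28, mean about 11).

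**Step 4: with covariates.** If covariates explain a share R² of the between-patient variance, φ becomes approximately φ(1 − R²).

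- R² = 0.3: 14.9% at m = 6, 50.5% at m = 28.
- R² = 0.5: 8.8% at m = 6, 43.0% at m = 28.
- R² = 0.8: φ = 0.53, 1.23 and 2.47 at m = 6, 14 and 28, giving about 0.7%, 8% and 21%.

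The last case is relevant because the implied intraclass correlation, (m × 0.2025/0.2484 − 1)/(m − 1), is 0.78 at m = 6 and 0.81 at m = 28. A single baseline CAM-ICU result would then explain about 80% of the between-patient variance. Simulating the Poisson model with baseline delirium status as a covariate gave about 1%, 11% and 19% at m = 6, 14 and 28, and roughly 8–13% with variable stays. If 40% of patients cannot be assessed at baseline (an assumption), the figures run from about 10% at m = 6 to 43% at m = 28.

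**Step 5: with the fix.** Robust standard errors at patient level gave about 4–6% in every scenario, with or without the covariate.

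**The case against.** The strongest reply concerns the covariates. The planned model is adjusted, and delirium subtype is among the covariates. The subgroup list in the same section defines the baseline delirium grouping to include patients without delirium. If the covariate has the same meaning, it carries baseline delirium status and removes much of the overdispersion. This stands. It rules out quoting 22–58% as the error rate of the planned regression, and it shows that with short stays the test could even be conservative. It does not rescue the model: the error then depends on length of stay and on how many patients are assessable at baseline, and the nominal 5% would be met only by chance.

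Second, the audit SD alone implies no range, because the number of assessments must be assumed. The 58% figure needs all 28 assessments for every patient. This also stands.

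Third, the rate comparison names no test and may be meant at patient level. A reader might infer an error of 37–69% for it, but that holds only if assessments are pooled as independent binomial trials, which the article does not say. The fair criticism is that its variance is unspecified.

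Fourth, the article condenses a fuller plan and mentions additional files that are not at hand, so a variance option might be stated there. But the article gives the model, the offset and every covariate for this analysis, and as stated that is an ordinary Poisson regression.

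Finally, the primary t test uses one percentage per patient and is sound. That stands and limits the severity.

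**Conclusion.** The point holds as a should-fix for a secondary analysis. The Poisson regression, as written, relies on a variance that the plan's own audit contradicts, with a dispersion of 2.6 at 6 assessments and 12.3 at 28 before adjustment. Its standard errors are therefore wrong.

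The effect on the type I error is a range, not one number:

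- Unadjusted: about 22–58% for 6–28 assessments, and about 9% at 3.
- Adjusted, with subtype carrying baseline status: about 1% at m = 6, about 20% at m = 28.
- The same, with 40% of patients unassessable at baseline: about 10–43%.

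These figures assume that the trial's between-patient spread resembles the audit's, that the stated numbers of assessments apply, and that counts behave like a beta-binomial.

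A reader might infer that the audit by itself proves a false-positive rate of 22–58% for the planned model, or that the trial's main conclusion is at risk. The document supports neither: the first ignores the planned covariates and the unknown number of assessments, and the primary test is unaffected.

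**What to change.** Keep the Poisson model, its offset and its covariates, and state that standard errors will be robust (sandwich) at patient level. A negative binomial, beta-binomial or binomial mixed model with a random patient effect would also serve. Name the test for the rate comparison and base its variance on patients rather than on single assessments. State whether delirium subtype as a covariate means baseline status with a category for no delirium.

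The same variance rule could be applied to the Poisson model for delirium- and coma-free days. That is precautionary, because the article gives no SD for that outcome.

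The cost is a sentence or two in the plan and one software option, with no new data or patients. Because the article was submitted before unblinding, the choice can be recorded without knowledge of the results. The downside is that confidence intervals will usually be wider.

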## Introduction

Delirium is a condition of acute organic brain dysfunction with disturbances of attention and cognition, a fluctuating course, and occurring as a direct consequence of an underlying medical condition [1]. It is particularly common in patients in intensive care units (ICU), with a wide range of prevalence reported in the literature (11–80%) [2–4]. Delirium in ICU is associated with poorer outcomes, including higher mortality, more time on a ventilator, increased length of stay (LOS), greater post-operative complications, increased need for tracheostomy, increased medical costs, and higher risk of dementia and cognitive impairment [3, 5–12].

Good quality sleep at night is recognised as an important aspect in the prevention and management of delirium. Melatonin is a natural hormone secreted by the pineal gland, which helps in the regulation of the sleep-wake cycle. Decreased melatonin levels and fluctuations in its metabolite, 6-SMT, have been associated with delirium in post-surgical and intensive care patients [13, 14].

It is possible that supplementing melatonin improves sleep and prevents delirium. A number of clinical trials of melatonin or melatonin agonists for the prevention of delirium have been performed to date [15–26]. It is difficult to draw firm conclusions due to conflicting results, methodological issues, and patient heterogeneity.

The ‘Prophylactic Melatonin for Delirium in Intensive Care’ is a multi-centre randomised double-blinded, placebo-controlled trial. The primary objective of this study is to determine whether melatonin given prophylactically decreases delirium in critically ill patients.

This study may provide evidence for a simple and effective agent to reduce delirium in patients admitted to the ICU.

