## Statistical principles

Differences will be considered statistically significant when *P* values are < 0.05, and 95% confidence intervals (95% CI) will be reported.

Adherence to protocol will be considered when patients have received all the required doses while in ICU and all the CAM-ICU assessments. This will be presented with descriptive statistics as a percentage and numerator and denominator. Protocol deviation is defined as lack of compliance with study drug administration or lack of assessment with CAM-ICU. All protocol deviations will be collated and presented in the results as descriptive statistics. All analyses will be conducted on both an intention-to-treat (ITT) and per-protocol (PP) basis. The ITT sample is defined as all randomised subjects including those who are lost to follow-up or have missing data. If the patient does not receive the assigned intervention post-randomisation, the patient will still be included in the ITT sample and analysed according to assigned treatment group.

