## Trial population

Screening data will be presented as descriptive statistics. Patients eligible to be considered for the study must be admitted to the ICU with an expected total LOS of at least 72 h, as determined by the treating intensivist. Eligible participants also must be able to be enrolled and treated within 48 h of being admitted to the ICU.

Exclusion criteria for participation in the study includes (1) patients aged < 18 years; (2) patients already on melatonin before their admission to ICU; (3) prior hypersensitivity reaction to any of the components of the study drug (melatonin, sucralose and glycerol, marshmallow flavour); (4) patients expected to be discharged within 72 h of their ICU admission; (5) expected/inevitable death within next 48 h; (6) pregnant or breastfeeding; (7) non-English speaking; (8) patients that are not expected to improve adequately to be able to be assessed with a CAM-ICU score during their ICU stay; (9) patients that are not able to be assessed due to neurological problems that would affect their ability to participate in a CAM-ICU assessment, as judged by treating physician; (10) no enteral route, as melatonin is not available in intravenous formulation; and (11) hepatic impairment defined as alanine transferase (ALT) > 500 IU/L, previous liver transplant, or liver cirrhosis categories Childs-Pugh B and C.

A CONSORT flow diagram will be presented. (Fig. 1) This will include the number of patients assessed for eligibility, excluded, randomised, allocated to each intervention arm, followed up, and analysed for each group. A report of withdrawals will be provided, describing the level at which they have occurred, the timing of withdrawals, and the reasons for the withdrawals.

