Finally, an analysis that looks at whether the individual reported a positive delirium assessment during their stay will be undertaken by comparing proportions between the groups through a logistic regression analysis controlling for variables including age, gender and length of stay.

The secondary outcomes to be analysed include (1) severity and duration of delirium, (2) sleep quality, (3) ICU and hospital length of stay;,(4) duration of mechanical ventilation, (5) mortality, and (6) economic analysis. Each secondary outcome will be adjusted for the same covariates as mentioned before: age, gender, delirium subtype, diagnostic category, and Pre-Deliric score.

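### The any-positive-assessment analysis includes patients already delirious at baseline, so a preventive effect on new-onset delirium is pulled toward no effect

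*SAP article*

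**What the plan says.** All places are in the SAP article.

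- **Aim.** Introduction: "The primary objective of this study is to determine whether melatonin given prophylactically decreases delirium in critically ill patients". Study methods: "The framework of the study is of superiority of melatonin over placebo for the prevention of delirium".
- **Who enters.** Trial population: "Eligible participants also must be able to be enrolled and treated within 48 h of being admitted to the ICU". None of the eleven exclusions listed there is delirium present at entry.
- **Baseline delirium is expected.** The third predetermined subgroup in Analysis is "percentage of delirium-free assessments by delirium subgroup at baseline: hyperactive, hypoactive, and mixed, as well as no delirium".
- **The analysis at issue.** The last delirium analysis before the list of secondary outcomes is "an analysis that looks at whether the individual reported a positive delirium assessment during their stay will be undertaken by comparing proportions between the groups", carried out "through a logistic regression analysis controlling for variables including age, gender and length of stay".
- **Contrast.** For the Poisson model of positive assessments, Analysis says: "The covariates will include age, gender, delirium subtype, diagnostic category, and Pre-Deliric score". The same list is carried over to the secondary outcomes. Delirium subtype is not named for the logistic model.
- **Population.** Statistical principles: "The ITT sample is defined as all randomised subjects including those who are lost to follow-up or have missing data". No narrower at-risk set is stated for the any-positive analysis.

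**The concern.** Delirium cannot be prevented in a patient who already has it. Such a patient will almost always have at least one positive assessment during the stay, whichever arm he or she is in. In a yes/no outcome of ever being positive, these patients add the same number of events per patient to both arms and carry almost no information on prevention.

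A reader who wants to know whether melatonin prevents delirium will look first at the proportions ever positive. If melatonin prevents new delirium, this comparison will understate the effect and may miss it. The baseline status needed to avoid this is already recorded.

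**Working it through.** **The plan's own figure.** The only sample size given for a delirium outcome is for the primary percentage: SD 45, difference 10 points, two-sided 5%, 80% power. The normal formula gives 2 × (1.960 + 0.842)² × 45² / 10² = 318, and the t-test version gives 318.8, so 319 per group is reproduced. Then 319 × 1.15 = 366.9 (367) and 367 × 1.15 = 422.05 (423). These figures are not disputed. The any-positive analysis has no sample size of its own.

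**Inputs.** From Study methods: 425 per arm, two-sided 5%. Assumed, because the SAP does not give them: b of 15%, 30% or 45%, and incidence among patients at risk of 40% on placebo and 30% on melatonin. All patients delirious at baseline are taken as events. The comparison is crude, without the covariates.

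**Formulas.**
- Pooled risk per arm: P = b + (1-b) × incidence, so the pooled risk difference is (1-b) × the difference in at-risk patients.
- z = difference / √[P₁(1-P₁)/n + P₂(1-P₂)/n], with n = 425 pooled and n = 425(1-b) at risk.
- At-risk odds ratio: (0.30/0.70)/(0.40/0.60) = 0.643.

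**Example, b = 30%.** Pooled risks are 0.30 + 0.70 × 0.40 = 0.58 and 0.30 + 0.70 × 0.30 = 0.51.
- Pooled: odds ratio (0.51/0.49)/(0.58/0.42) = 0.754; z = 0.07/√[(0.2436 + 0.2499)/425] = 2.05.
- At risk, n = 297.5: z = 0.10/√[(0.24 + 0.21)/297.5] = 2.57.

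| b | Pooled risks | Pooled OR | Pooled z (power) | At-risk OR | At-risk z (power) |
|---|---|---|---|---|---|
| 15% | 49.0% v 40.5% | 0.71 | 2.50 (71%) | 0.64 | 2.83 (81%) |
| 30% | 58.0% v 51.0% | 0.75 | 2.05 (54%) | 0.64 | 2.57 (73%) |
| 45% | 67.0% v 61.5% | 0.79 | 1.68 (39%) | 0.64 | 2.28 (63%) |

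**Other incidence assumptions, b = 30%.**

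| Incidence | At-risk OR | Pooled OR | Pooled power | At-risk power |
|---|---|---|---|---|
| 30% v 22.5% | 0.68 | 0.81 | 33.4% | 54.8% |
| 40% v 32% | 0.71 | 0.80 | 37.5% | 53.0% |
| 50% v 37.5% | 0.60 | 0.69 | 74.3% | 87.0% |

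**Two checks on the assumptions.**
- If 10% of patients delirious at baseline never test positive on trial, the pooled odds ratios are 0.71, 0.76 and 0.80, almost unchanged.
- Study methods expects up to 10% never to be assessable. If these are spread evenly, every z is multiplied by √0.9 = 0.949: pooled 2.37, 1.95 and 1.59; at risk 2.69, 2.44 and 2.16. The absolute values above are therefore somewhat optimistic, but the ordering does not change.

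**The case against.** Several points on the other side are sound.

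- **Separating prevention from resolution.** A reader might infer that the trial cannot tell prevention of new delirium from faster resolution of existing delirium. The documents do not support that. The third subgroup already estimates the primary percentage separately in patients without delirium at baseline, so a preventive effect can be seen there.
- **The primary outcome.** The percentage of delirium-free assessments measures burden and can improve by either route. That fits the stated objective of decreasing delirium, and the abstract also speaks of its rate and severity. The word prevention in the superiority sentence does not make the primary comparison invalid.
- **The 10-point target.** A reader might also take this as an effect in at-risk patients only, which pooling would dilute to 8.5, 7.0 or 5.5 points. Study methods sets the target for the trial population as a whole and does not describe the audit patients as free of delirium at entry. The dilution would come from changing the design assumption.
- **A minor analysis with an open covariate list.** The analysis is one of several supporting ones, and its covariates are introduced as examples. The subgroup paragraph, too, applies to outcomes where appropriate. Both leave room to handle baseline delirium, but neither fixes it for this analysis, and a plan published before unblinding is the place to do so.
- **Patients not assessable at baseline.** Exclusion 8 removes only those not expected to become assessable during the stay, so some patients will be neither positive nor negative at entry. This stands: restricting to CAM-ICU negative patients would silently drop them, and the at-risk sample sizes above treat everyone who is not positive as retained and truly at risk. If some of those not assessable were already delirious, part of the dilution would remain.

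**Conclusion.** The point holds for the any-positive analysis. It pools patients who can no longer have delirium prevented with those who can, and it does not name baseline delirium as a covariate. The direction, toward no effect, follows for any b above zero when patients delirious at baseline are events in both arms. The size cannot be fixed from the SAP. With 40% against 30% incidence and b between 15% and 45%, the odds ratio moves from 0.64 to between 0.71 and 0.79. Under these assumptions the restricted analysis has the larger expected z despite fewer patients.

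The point does not extend to the primary comparison, nor to a claim that the trial is unable to study prevention. It is a worthwhile, inexpensive improvement to a supporting analysis and to how the results are worded.

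**What to change.** In Analysis, change the any-positive paragraph as follows.

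1. Define the outcome as new-onset delirium in patients not CAM-ICU positive at baseline. Count only assessments after the first scheduled dose time, by the same rule in both arms.
2. State in advance how patients not assessable at baseline are handled, for example kept in the main version and left out in a sensitivity version.
3. Report the numbers positive, negative and not assessable at baseline by arm.
4. Keep the all-randomised version alongside. Merely adding baseline delirium as a covariate is not a real alternative: if every baseline-positive patient is an event, the covariate predicts the outcome perfectly in that stratum, which amounts to the same restriction.
5. Rest any statement about prevention on this analysis and on the no-delirium level of the third subgroup. Describe the all-randomised primary result as an effect on delirium burden.

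The cost is SAP wording and one further analysis set from data already collected. Baseline status precedes treatment, so the randomised comparison is kept within the restricted set. The article states that it was submitted before database lock and unblinding, when the change can be made without knowledge of results. The downside is a smaller sample for the new-onset estimate.

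### The supporting logistic model for any positive delirium assessment controls for length of stay, a post-randomisation trial outcome, so its odds ratio need not estimate the effect of assignment

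*SAP article*

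**What the plan says.** After the primary t test and the Poisson rate model, the Analysis section of the SAP article adds a third delirium analysis. Its outcome is "whether the individual reported a positive delirium assessment during their stay", and the arms are compared by "a logistic regression analysis controlling for variables including age, gender and length of stay".

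Other parts of the article bear on that covariate:

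- **Analysis, list of secondary outcomes:** item (3) is "ICU and hospital length of stay".
- **Study methods, sample size:** the investigators wanted the study "powered to detect a reduction of LOS of 1 day", and give as a reason that "a significant relationship between delirium and LOS has been observed".
- **Analysis, primary outcome:** "patients will be assessed for delirium twice a day for 14 days or until they are discharged from ICU, whichever occurs first". Stay therefore also sets how many chances a patient has to test positive.
- **Analysis, Poisson model:** "The covariates will include age, gender, delirium subtype, diagnostic category, and Pre-Deliric score". These are introduced as baseline characteristics, and the number of assessments enters as an offset.

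**The concern.** A covariate in a randomised comparison should be fixed before treatment can act on it. Length of stay is not. On the plan's own premises, treatment may change it and delirium is related to it. If delirium prolongs stay, the model conditions on a consequence of its own outcome. Comparing melatonin and placebo patients who ended with the same stay is no longer a comparison of randomised groups.

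At stake is the only planned analysis of whether a patient had any delirium at all. Readers are likely to take its odds ratio as the effect of melatonin on the occurrence of delirium. As specified, it may not be that.

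**Working it through.** **1. The plan's own figures.** The plan attaches no number to this model. Its primary sample size is not in dispute: 2 × (1.960 + 0.842)² × 45² / 10² gives 318 per group, against 319 stated.

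**2. Is the covariate post-randomisation?** Patients are enrolled and treated within 48 h of ICU admission and then followed until discharge, so total stay is settled after allocation. Nothing in the article limits the covariate to stay before randomisation, gives a reason for it, or plans this model without it. The companion Poisson model also uses a post-randomisation quantity, the number of assessments, but as the denominator of the rate it reports and not as a covariate.

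**3. What conditioning does.** Let D be any positive assessment, T the arm (1 = melatonin) and L the stay. By Bayes' rule, odds(D | T, L) = odds(D | T) × f(L | D=1, T) / f(L | D=0, T). Hence

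OR at stay L = OR of assignment × R(L), where R(L) is the ratio f(L | D=1) / f(L | D=0) in the melatonin arm divided by the same ratio in the placebo arm.

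- If treatment changes stay only through delirium, f(L | D) is the same in both arms and R = 1. Unmeasured severity disturbs this only slightly (step 4).
- If treatment also changes stay by another route, R differs from 1.

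Example with assumed inputs: gamma stay with shape 2, means (not delirious, delirious) of 5 and 7 days on placebo, and 4 and 6 days on melatonin. The gamma ratio is (m0/m1)² × exp{2L(1/m0 − 1/m1)}, so

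R(L) = [(4/6)² / (5/7)²] × exp{L × (0.1667 − 0.1143)} = 0.871 × exp(0.0524 L).

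This gives R(2) = 0.97, R(5) = 1.13 and R(10) = 1.47. The distortion varies with stay. If melatonin lengthened stay by another route, exchanging the arms would invert R.

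**4. Simulation.** None of these inputs comes from the documents: 50% control risk of any delirium; standard normal unmeasured severity with log-odds 0.5 per SD on delirium; gamma stay with shape 2 and mean 5·exp(0.3 × severity), plus 0 to 4 days if delirious, minus 0 to 1 day directly from treatment. There were 300,000 patients per setting.

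With no true effect on delirium, the odds ratio without stay was 0.98 to 1.01 throughout. With stay in the model:

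| Days added by delirium | No direct effect on stay | 0.5 day shorter | 1 day shorter |
|---|---|---|---|
| 0 | 1.00 | 1.02 | 1.03 |
| 1 | 1.01 | 1.05 | 1.10 |
| 2 | 1.00 | 1.05 | 1.15 |
| 4 | 1.00 | 1.09 | 1.20 |

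With a conditional odds ratio of 0.67 (0.68 to 0.69 without stay), the adjusted value was 0.67 to 0.69 with no direct effect on stay and 0.72 to 0.82 with a 1-day direct effect.

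**5. Rejection at the 5% level, 425 per arm, 1,500 trials per setting.**

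| True odds ratio | Days added by delirium | Direct effect on stay | Without stay | With stay |
|---|---|---|---|---|
| 1.00 | 2 | 1 day shorter | 5% | 14% |
| 1.00 | 4 | 1 day shorter | 5% | 23% |
| 0.67 | 2 | none | 78% | 77% |
| 0.67 | 2 | 1 day shorter | 76% | 37% |

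**6. When stay drives detection.** The model in steps 4 and 5 does not let a longer stay create more chances to test positive. A further simulation did, with no effect per assessment, mean stay of 5.5 against 4.5 days and about 50% control incidence (again assumed).

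| Model | Odds ratio | Significant |
|---|---|---|
| Without stay | 0.82 to 0.86 | 18% to 34% |
| With stay, delirium does not prolong stay | 1.06 to 1.15 | 5% to 14% |
| With stay, delirium adds 2 days | 1.23 to 1.36 | 17% to 26% |

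**The case against.** The best defence is unequal opportunity. A patient who leaves early is tested less often, so a treatment that shortens stay would lower the share ever testing positive even with no effect on the brain. Step 6 shows that this is real: omitting stay gives 0.82 to 0.86 under a null effect per assessment. That result is still a valid effect of assignment on detected delirium, but it is not an effect per unit of exposure. The defence does not rescue the covariate, because the adjusted odds ratio is also off the null in the same setting, at 1.06 to 1.36. It does mean that dropping stay has a price, which should be stated.

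Three further objections stand and limit the point:

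- **Certainty.** A reader might infer that the adjusted odds ratio is biased, and biased towards harm or no effect. The documents do not support that. The distortion needs a route from melatonin to stay other than through delirium, and the article gives no figure for one. Without it, the simulated bias was negligible.
- **Omitted predictors.** A reader might infer that the model leaves out baseline delirium, diagnosis and Pre-Deliric score. The covariate list is open-ended, so the text does not show this. Omitting prognostic baseline variables would in any case not undermine the randomised comparison.
- **Rank.** This is the third delirium analysis. It is not the primary outcome, was not used for the sample size, and is not in the numbered list of secondary outcomes.

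The article also does not say whether ICU or hospital stay is meant. The ICU reading fits the assessment window, and the criticism is the same for either.

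**Conclusion.** The point holds as a should-fix. The model controls for a variable that is measured after randomisation, is itself a trial outcome, and on the plan's own account is related to delirium and may be shortened by treatment. Its odds ratio need not estimate the effect of assignment.

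The amount and direction of bias cannot be derived from the documents. Under the assumed inputs of step 4, the null odds ratio ranges from 1.00 (no other route to stay) to 1.20 (1-day direct effect, delirium adding 4 days). These figures are illustrations, not estimates for this trial.

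A reader might also infer that the trial's main conclusion is at risk. It is not: the primary t test does not involve length of stay, and its supporting regression and the Poisson model adjust for baseline covariates.

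**What to change.** In the Analysis section:

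1. Remove length of stay from the logistic model. Adjust only for the baseline covariates already named for the Poisson model: age, gender, delirium subtype at baseline, diagnostic category and Pre-Deliric score.
2. State that the odds ratio is the effect of assignment on any delirium detected during the ICU stay, since assessment stops at ICU discharge or day 14.
3. Refer to the existing Poisson model, with its offset, for the rate per assessment.
4. If a version adjusted for length of stay is still wanted, label it exploratory and say that it is not a randomised comparison.

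The cost is wording only, with no new data and no change in sample size. The Trial status section says the SAP was submitted before follow-up was complete and before unblinding; the change should likewise be dated before unblinding, or reported as a later change. The small downside is that, without length of stay, the odds ratio also reflects any difference between the arms in time at risk.
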